## **4.2 Aims of the study**

The first specific aim of this project is to explore the knowledge stage as well as the attitudes, needs and anxieties towards pregnancy among MS and SLE patients and their physicians or healthcare employees. Therefore, two systematic reviews (one for MS and one for SLE) will be conducted in this area. In the next step, a new questionnaire will be developed (questionnaire on motherhood/ pregnancy choice and worries, MPWQ). A second questionnaire addressing knowledge will be translated and revised (motherhood choice knowledge questionnaire – revised, MCKQ-R). Both questionnaires will be tested for feasibility and validity in cross-sectional studies.

The further steps of the intervention will focus exclusively on MS.

The following feasibility testing and the pilot of the DST and the DCP will give an idea whether the decision coaching programme on motherhood choice or simply providing a decision aid is best suited for decision-making. We hypothesise that the decision aid plus coaching will lead to more positive (e.g. lower decisional conflict, (Buchholz, 2011)) outcomes than the decision aid alone. But we also recognise potential barriers as for example that the coaching is provided by an external nurse and that the coaching will require new resources.

### 4.3 Design

A multiphase mixed methods study (Creswell & Plano Clark, 2011) will be conducted to develop and evaluate the multicomponent programme. Qualitative and quantitative methods will be used intentionally to acquire a comprehensive impression of study processes. The study conduct will be based on the MRC framework for developing and evaluating complex interventions (Craig et al., 2008; Moore et al., 2015) for a step-wise approach. In phase 1, we will stepwise develop the DST and DCP. For this reason, we will conduct systematic reviews on particular topics (see 5.1) as well as qualitative interviews. Further, we will develop, adapt and validate questionnaires. In phase 2, the feasibility testing of the developed decision support tool and the decision coaching programme will follow (Arañ, Campbell, Cooper, & Lancaster, 2010; Eldridge et al., 2016) including a qualitative feasibility testing as well as a randomised pilot.

[figure not shown]

Figure 1- particular steps in both the development and feasibility testing phase.

The project will be based on the UK MRC frameworks for developing and evaluating complex interventions (Craig et al. 2008; Moore et al. 2015) (phase 1 and 2).

The “Throughput-Model” lays the foundation for a continuous optimisation of care by considering the complexity of interventions and context factors (input) as well as the observation process (throughput) when defining intervention outcomes (Pfaff et al., 2017b). This project mainly focusses on input by the development of a complex intervention. The intervention addresses patients, but also nurses are involved as they are trained to deliver the intervention. The context factors are specifically addressed by an accompanying process evaluation (Graham F. Moore et al., 2015). Throughput will be addressed by qualitative and quantitative measures as described under specific aim 2. Outcomes will be tested and further defined by the feasibility study. Further, the feasibility phase will help to explore the output and based on the analysis, the input may be modified within a future randomised clinical trial (RCT).

### 4.4 Study process

The study consists of 2 phases and 8 steps. Study steps 1 - 4 will address MS and SLE. The following study steps 5 – 8 will focus on MS (see Figure 1). Therefore, the project stops for SLE after the web-based survey.

## 5 Research plan and methods

Overall, the project is guided by the principles evidence-based medicine (Sackett, Rosenberg, Gray, Haynes, & Richardson, 1996) and evidence-based health information (Lühnen J., 2017) as well as the concepts of SDM (Elwyn et al., 2001a) and decision coaching (Stacey, Kryworuchko, et al., 2013). The "Theory of Planned Behaviour" (Ajzen, 2011), which was already used in earlier studies, forms the overall theoretical basis concerning behavioural psychology.

[figure not shown]

Figure 2- Specifying the study steps concerning the two different autoimmune disorders multiple sclerosis (MS) and systemic lupus erythematosus (SLE). DA= Decision Aid.

In phase 1 - development of the outcome measures and the intervention programmes will take place (steps 1-5) and in phase 2 the feasibility of the decision support tool and the decision coaching programme will be tested (steps 6-7, figure 2).

### 5.1 Systematic Reviews

#### 5.1.1 Procedure

As a first step, systematic literature reviews on MS and SLE will be conducted to explore all available qualitative and quantitative data on patients' knowledge and attitude towards pregnancy as well as their needs on family planning. This includes various issues like the influence of a patient's pregnancy to the course of MS/SLE, the meaning of the social environment and also the aspect of career. Additionally, the evidence on immunotherapies in particular with

regard to (a future) pregnancy and lactation period in women with MS/SLE will be reviewed. Nevertheless, the effect of fertility treatment, e.g. regarding the course of MS/SLE, will be explored.

Therefore, literature searches will be performed in MEDLINE (via Ovid) according to defined questions using PICO and variants as well as defined study selection criteria. Two reviewers will screen the findings (title/abstract), identified full-texts and perform a risk of bias evaluation of included studies. Subsequently, the data extraction of the identified studies will follow by one researcher. Another researcher will control the extracted data. Endnote and Rayyan will be used for bibliographic management and screening.

### **5.1.2 Expected results**

The systematic reviews of the relevant literature will provide the evidence base for the patient interview and questionnaire development outlined below.

## **5.2 Qualitative Interviews**

### **5.2.1 Study setting**

Focus groups (FG) with women with MS/SLE will be conducted by two researchers (JP and AR) in different centres (e.g. Bochum and Hamburg for MS and Düsseldorf and Hamburg for SLE). In addition, personal in-depths interviews with patients, patient representatives, neurologists and rheumatologists will be performed by telephone.

### **5.2.2 Participants**

The focus groups and the personal interviews will be conducted with women with MS and SLE aged 18-45 years considering motherhood, being pregnant, or parenting. Only persons, who are fluent in German and have provided signed informed consent will be included.

Neurologists and rheumatologists will be eligible to participate when they have a special expertise (MS or SLE) and have provided signed informed consent.

### **5.2.3 Procedure**

The structured interview guidelines will be developed based on the results from the literature searches and other materials as for example the Australian decision aid on motherhood choice (M. Prunty et al., 2008). One interview guide will address experiences, counselling and information needs as well as concerns of women with SLE/MS to be used in focus groups and personal interviews and the other one will address physician's perception regarding motherhood in MS/SLE.

Before starting the focus group and the personal interviews, the participants have to provide informed consent and to fill a short questionnaire collecting demographic data and some specific information. Each interview will be audio-recorded and transcribed verbatim.

### **5.2.4 Expected results**

The analysis will provide important information on information needs, experiences and concerns of women with MS/ SLE and the perception of experts on the topic. The thematic analysis will lead to the development/ revision of the questionnaires and will provide important information for the development of the decision support tool and the decision coaching programme.

### **5.2.5 Sample Size**

Each focus group meeting will consist of 5-10 participants plus two moderators. It is planned to have two focus groups with women with MS and two with women with SLE. The personal interviews will be conducted with women with MS (n=5) and SLE (n=5), with neurologists (n=3) and rheumatologists (n=3).

### **5.2.6 Recruitment**

Participants for the focus group meetings and the interviews will be recruited from the MS clinic at the University Medical Center Hamburg Eppendorf (UKE, Universitätsklinikum Hamburg-Eppendorf), the MS pregnancies registry at the Joseph Hospital in Bochum (MS) and the SLE registry of the University Medical Center Düsseldorf (UKD, Universitätsklinikum Düsseldorf) (SLE). The physicians will be recruited throughout Germany.

### **5.2.7 Participant timeline**

The focus groups interviews will take about 90 minutes. The personal interviews will be scheduled for 30-60 mins.

### **5.2.8 Data analysis and statistical methods**

A qualitative thematic content analysis (V. Braun & Clarke, 2014) using deductive and inductive categories will be performed by JP. The phases of the thematic analysis include: 1) familiarisation with the data, 2) generalising initial codes, 2) searching for themes, 4) reviewing themes, 5) defining and naming themes and 6) producing the report (V. Braun & Clarke, 2014). A computer-assisted qualitative data analysis software (MAXQDA 2018) will be used to manage and organise the data.

## **5.3 Questionnaire development and translation**

### **5.3.1 Study setting**

Two cross-sectional studies will be performed with women from the MS pregnancies registry in Bochum (PD [name]) and SLE registry in Düsseldorf ([name]. [name]) to test the developed questionnaire and gather further information on information needs. The conduction of the studies will be web-based.

### **5.3.2 Participants**

The cross-sectional studies will include women (18– 45 years) with MS/SLE considering pregnancy. Only persons, who state that they are fluent in German and who have provided signed informed consent will be included.

### **5.3.3 Procedure**

The motherhood choice knowledge questionnaire (M. Prunty et al., 2008) will be revised and translated (MCKQ-R) based on the literature reviews and interviews. In addition, based on the qualitative data obtained in the interviews and the results of the literature reviews, a questionnaire on motherhood/pregnancy choice and worries (MPWQ) will be developed. Both questionnaires will be qualitatively evaluated with think-aloud (Jaspers, Steen, van den Bos, & Geenen, 2004) and teach back methodology and refined. Afterwards, the questionnaire will be piloted in cross-sectional studies to test basic psychometric properties. The studies will be performed using UNIPARK (UNIPARK & QuestBack, 2019), a widely established web-based

survey methodology and will be conducted according to appropriate reporting (Eysenbach, 2004).

#### **5.3.4 Expected results**

The analysis of the cross-sectional studies will lead to a final version of two different questionnaires for women with MS/SLE considering motherhood. The first one is the motherhood choice knowledge questionnaire (**MCKQ-R**) MS/SLE and the second the motherhood/pregnancy choice and worries questionnaire (**MPWQ**). Further, additional questions on information needs of women with SLE/ MS will be used to plan intervention programmes according to the needs of women with MS/ SLE.

#### **5.3.5 Sample Size**

Both cross-sectional studies will include about 100 participants.

#### **5.3.6 Recruitment**

Participants will be recruited via the MS pregnancies registry Joseph Hospital in Bochum (MS) and the SLE registry of the UKD Dusseldorf (SLE) via mailing lists. Informed content and the cross-sectional survey will be conducted online via UNIPARK.

#### **5.3.7 Participant timeline**

The mean duration of the participation in the cross-sectional study will take about 45 minutes.

#### **5.3.8 Data analysis and statistical methods**

The raw data of the cross-sectional studies will be exported from the online database UNIPARK. Data analysis will be performed with the software programme SPSS (version 24/25) and demographic data will be analysed using descriptive statistics.

The newly developed questionnaires will be evaluated for their psychometric properties using standard procedures as previously described (Gold et al., MSJ 2001) and modified if necessary. This includes assessments of item difficulty and score distributions (floor/ceiling effects), reliability (internal consistency) and aspects of validity (construct validity, convergent and discriminatory validity). An item analysis is planned to determine the item difficulty, item discriminatory power and item distribution. Values between 0.20 and 0.80 are expected for the item difficulty, and the item discriminatory power should be between 0.40 and 0.70. For the determination of the internal consistency of the questionnaire, Cronbach's alpha will be calculated; hereby, for a high internal consistency of the test, the values should be above 0.70. Reproducibility over time will be assessed by Pearson product moment and intraclass correlations (ICC). Appropriateness of the questionnaires will be tested by examining score distributions and floor/ceiling percentages on each scale. In general, a percentage of less than 20% is considered satisfactory. Construct validity will be assessed by exploratory factor analysis (Bühner, 2006).

## **5.4 Web-based survey**

### **5.4.1 Study setting**

Two web-based surveys will be conducted across Germany in cooperation with patient organisations the German Multiple Sclerosis Society (DMSG, Deutsche Multiple Sklerose Gesellschaft) and Lupus Selbsthilfe e.V.), who will inform about the survey on their websites. The studies will be performed using UNIPARK.

### **5.4.2 Participants**

The participants will be women with MS/SLE considering pregnancy at child-bearing age between 18 and 45 years. Available internet access is mandatory. Only persons, who state that they are fluent in German and who have provided signed informed consent will be included.

### **5.4.3 Procedure**

These web-based surveys including the MCKQ-R and the MPWQ will clarify worries and concerns but also the knowledge of women with MS and SLE regarding pregnancy. The survey will be conducted using UNIPARK and will consist of a demographical and disease specific section, followed by the MCKQ-R, the MPWQ and the Decisional Conflict Scale (DCS) (Buchholz, 2011). In addition, a slightly modified version of the Control Preference Scale (CPS) (Degner, Sloan, & Venkatesh 1997), the Pregnancy-Related Anxiety Questionnaire-Revised 2 (PRAQ-2) (Mudra et al. 2019) and the extension of the Leipzig Questionnaire of Motives to have a Child (LKM) (Ernst, Brähler, Wild, Faber, Merzenich, & Beutel 2020) will be included. Degner, L. F., Sloan, J. A., & Venkatesh, P. (1997). The control preferences scale. Canadian Journal of Nursing Research Archive, 29(3).

### **5.4.4 Expected results**

The web-based survey will on the one hand clinically validate the MCKQ-R and the MPWQ and on the other hand gathering the percentage of women with MS and SLE considering pregnancy as well as their worries, concerns, knowledge and decisional conflict (explored with the MCKQ-R, DCS, and the MPWQ). Therefore, patient reported outcome measurements for an intervention on elaborating motherhood choice in MS and SL are available after the analysis.

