### **5.4.5 Sample Size**

Each web-based survey will include at least 100 women with MS/SLE at the childbearing age (18-45 years) considering pregnancy.

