### **5.4.6 Recruitment**

The participants recruited via the websites of the DMSG and Lupus Selbsthilfe e.V. In addition, centres and local self-help organisations will be asked to inform potential participants via mailing lists.

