### **5.8.2 Participants**

The participants for the survey and qualitative evaluation with think-aloud will be women with multiple sclerosis (MS) at child-bearing age between 18 and 45 years. Women who either have

already at least one child or who are dealing or have dealt with the issue motherhood are eligible to participate. Available internet access is mandatory for the web-based survey. Only women who indicate that they are fluent in the local national language and who have provided signed informed consent will be included.

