### 5.8.4 Expected results

The web-based survey will on the one hand validate the MCKQ-R and the MPWQ for the participating countries. On the other hand, the survey will be gathering the percentage of women with MS considering pregnancy as well as their worries, attitude, knowledge and decisional conflict across the different countries (explored with the MCKQ-R, DCS, and the MPWQ). Therefore, cross-country insights and differences about motherhood and MS can be identified.

Based on the results of an international study on the risk knowledge level in people with relapsing-remitting MS, we expect that the knowledge level about MS and motherhood/pregnancy will be moderate in all participating countries. Generally, we hypothesise that a higher knowledge level is associated with women who are currently considering a pregnancy or are already pregnant compared to women who have already children, because the issue of motherhood and MS is more present in these women.

Regarding the results of the MPWQ, we expect different results in each country for the possible scales attitudes, concerns as well as coping strategies. Depending on the country, there might be participants who will be more concerned or have more coping strategies in relation to participants from the other countries. In general, we assume that participants who have already had at least one child after the MS diagnosis will be less concerned, have more coping strategies and a more positive attitude towards MS and motherhood compared to childless women or women considering pregnancy.

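### The German web surveys (5.4) promise the percentage of women considering pregnancy but enrol only such women; in the multinational survey (5.8) that percentage is only a share of selected respondents

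*Protocol*

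**What the plan says.** **German surveys (step 4).** Section 5.4.4 names two products. One is validation of the two questionnaires. The other is "gathering the percentage of women with MS and SLE considering pregnancy as well as their worries, concerns, knowledge and decisional conflict". On eligibility, 5.4.2 states: "The participants will be women with MS/SLE considering pregnancy at child-bearing age between 18 and 45 years". Section 5.4.5 sets the size: "Each web-based survey will include at least 100 women with MS/SLE at the childbearing age (18-45 years) considering pregnancy". Recruitment (5.4.6) is by notices on the two patient organisations' websites, with mailing lists from centres and local groups in addition. No count of women approached or screened is described.

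**Multinational survey (step 8, MS only).** Section 5.8.4 makes a parallel promise, to be reported across countries: "the survey will be gathering the percentage of women with MS considering pregnancy as well as their worries, attitude, knowledge and decisional conflict". Eligibility is wider. Under 5.8.2, women aged 18-45 who have "already at least one child or who are dealing or have dealt with the issue motherhood are eligible to participate". Section 5.8.5, however, describes the minimum of 50 survey participants per country as women considering pregnancy. Recruitment (5.8.6) is primarily through local self-help organisations, and MS outpatient clinics also inform women about the survey.

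**The concern.** A percentage carries information only if the sample could contain women on both sides of the question. In step 4 the characteristic to be estimated is also the condition for entry, so the survey cannot deliver one of its two stated results. In step 8 both kinds of women can enter, but childless women who have never dealt with motherhood cannot. The percentage then depends on the entry rule and on who responds to the notices.

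What is at stake is interpretation. Section 7.7 plans a journal publication of the web-based survey and gives a summary on the German MS Society's website as an example of wider dissemination. A figure labelled in the words of 5.4.4 or 5.8.4 would invite reading as the share of all women with the disease who are considering pregnancy. In step 8, a difference between countries could also reflect differences in who was eligible and who volunteered.

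**Working it through.** The protocol states no expected percentage and no precision target for it, so there is no figure to reproduce. The check is on numerator and denominator.

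**Notation**
- p: true share of women aged 18-45 with the disease who are considering pregnancy. The protocol gives no value; 10%, 30% and 50% are assumed below.
- m: share who meet the entry rule but are not now considering pregnancy. The protocol gives no value.
- Share among eligible women = p / (p + m). This takes every woman considering pregnancy as eligible and ignores volunteer effects.

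**Step 4, under 5.4.2 and 5.4.5**
- The entry rule is considering pregnancy, so m = 0.
- p = 10%: 0.10 / 0.10 = 100%.
- p = 30%: 0.30 / 0.30 = 100%.
- p = 50%: 0.50 / 0.50 = 100%.
- With the minimum sample this is 100 of 100 in each survey. A lower result would only count respondents who should not have been enrolled.

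Could another section supply the denominator? Section 5.4.3 lists a demographic and disease-specific part, but any intention item in it would be answered only by women already selected on that answer. Section 5.4.6 describes no sampling frame. Section 5.4.8 refers to 5.3.8, which covers psychometric properties and descriptive demographics. None of them does.

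**Step 8, under 5.8.2**
- Mothers and women who dealt with the issue in the past may enter without now considering pregnancy, so m can exceed 0 and the share can vary.
- At an assumed p = 30%:
  - m = 10%: 0.30 / 0.40 = 75%.
  - m = 30%: 0.30 / 0.60 = 50%.
  - m = 50%: 0.30 / 0.80 = 37.5%.
- Over p and m each from 10% to 50%, the share runs from 0.10 / 0.60 = 16.7% to 0.50 / 0.60 = 83.3%.

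These values show two things only: the share is not a constant, and the same p can give different results when m differs. They do not estimate the bias, because nothing in the protocol fixes p or m, and self-selection could move the result either way.

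**Step 8, if the wording of 5.8.5 governed entry**
- m = 0 and the share is again 100%. The two sections therefore imply different things about the same percentage.

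**The case against.** The strongest reply is that this is half a sentence under expected results. The percentage is absent from the synopsis objectives and from the aims in 4.2. No sample size is derived from it, and neither 5.3.8 (which 5.4.8 adopts) nor 5.8.8 specifies an estimate, interval or test for it. Validation, the description of decisional conflict and the pilot do not use it. All of this stands, and it keeps the severity low. It does not remove the contradiction in step 4, where a stated result cannot be produced, and no later analysis plan can restore women who were never enrolled.

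A second reply is that the clause means only the worries and knowledge of women considering pregnancy. The sentence lists the percentage first and the other measures after it, and 5.8.4 repeats that structure, so this reading is strained.

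For step 8 the reply has more force. Section 5.8.2 deliberately admits a mixture, and the hypotheses in 5.8.4 compare women considering pregnancy with women who already have children. Describing how the sample divides is legitimate and needed for those comparisons. The minimum of 50 in 5.8.5 can also be read as a floor within the wider sample. This stands: in step 8 the fault lies in the label, not in collecting the figure.

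**Conclusion.** The point holds fully for step 4: as written, the percentage promised in 5.4.4 is 100% by construction for both MS and SLE. This rests only on 5.4.2 being applied as stated.

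For step 8 it holds in a limited form. The percentage can vary, but it is conditional on having a child or having dealt with motherhood, and on recruitment mainly through self-help organisations. It is a share of respondents, not the percentage of women with MS considering pregnancy, and it cannot be compared across countries as the latter.

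A reader might infer three stronger things that the protocol does not support:
- That the step 8 percentage is also fixed by eligibility. This follows only if the wording of 5.8.5 overrides 5.8.2.
- That the step 8 percentage is inflated by a particular factor. The protocol gives no size for the excluded group and no basis for the net effect of volunteering.
- That the surveys are invalid. The psychometric validation does not need this percentage, and the randomised pilot is separate.

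Severity is minor to moderate: wrong as written, confined to one secondary output, and cheap to correct.

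**What to change.** **5.4.4.** Delete the percentage of women considering pregnancy and keep the worries, concerns, knowledge and decisional conflict of the women enrolled. This costs wording only.

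If the percentage is wanted, open the step 4 survey to all women aged 18-45 with the diagnosis, record pregnancy intention as an item, keep the step 4 validation analyses in those considering pregnancy, and report the figure only as a share of respondents. This costs one item, a wider eligibility sentence and an amendment under 7.2. The minimum of 100 should then refer to the women considering pregnancy, so total recruitment rises; at an assumed 50% of respondents it would be 100 / 0.5 = 200 per survey. Self-selected recruitment would still rule out a population figure.

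**5.8.4.** Keep the figure, but label it as the share of survey respondents considering pregnancy, given as sample composition by country and not as a country comparison of women with MS. This costs wording only.

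**5.8.2 and 5.8.5.** Reconcile them: state whether the 50 per country counts all eligible respondents or only those considering pregnancy. The step 8 validation should not be restricted to women considering pregnancy, because that would contradict 5.8.2.
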